#### Inclusion and exclusion criteria

Health consumers who are aged 16 years of age and over who present to an emergency department with significant suicidality will be considered for the Aftercare intervention. They will be ineligible to participate if they are admitted to the hospital as an inpatient, if they are being actively case managed by the local health district’s mental health services, or if they have cognitive impairment sufficient to preclude full participation in, or comprehension of, the intervention as assessed by the referring clinician.

### Study procedure

Health consumers attending their local emergency department following a suicide attempt or at high risk for suicide are provided with a mental health assessment by clinical staff, where risk for suicide (and therefore suitability for the Aftercare intervention) is determined by standard hospital mental health assessment protocols. Staff determine whether the consumer warrants admission to hospital, as per the NSW Ministry of Health policies. If the consumer is not admitted to hospital as an inpatient, standard procedures include one follow-up phone call or home visit by the local health district’s mental health outreach team within seven days and a discharge letter to the person’s general practitioner. If the consumer is eligible for referral to the Aftercare service he/she will also be given a brief overview of the service by an emergency department clinician and at that time may choose to provide verbal consent to be referred to the service. The emergency department staff will contact the Aftercare service by phone and provide a referral. The participant flow process is shown in Fig. 1.

**Fig. 1 Fig1:**
[figure not shown]
Participant Recruitment

#### Aftercare intervention

The Aftercare service is administered through a collaboration of three community-based organisations in the region; Grand Pacific Health, Flourish Australia and the South Coast Medical Service Aboriginal Corporation. Referrals are taken by Grand Pacific Health and allocated according to location.

The consumer will be contacted by an Aftercare peer worker within one hour of the referral being received from the emergency department, while the consumer is still in the emergency department; or if the referral is made outside of operational hours they will be contacted the following day. A brief overview of the Aftercare program will be provided and, with consent, an initial community-based appointment with an Aftercare mental health clinician will be scheduled for the following day, or otherwise, as best convenient for the participant within the shortest possible timeframe.

Participants of the Aftercare service will attend the community-based service for their first appointment. Prior to their appointment, they will be provided with the research participant information sheet and consent form, and will have the opportunity to discuss the research further. Following this, they will complete the pre-intervention measures via tablet computer (or using pen and paper when appropriate).

The initial appointment with a mental health clinician will involve a collaborative assessment and planning session and take approximately one hour. The assigned peer worker will also be present and, with the consent of the participant, the participant’s family/carer will be encouraged to attend. Participants will complete the Suicide Status Form-4 (SSF-4) [53] with the mental health clinician. The SSF-4 is a multi-component clinical semi-structured assessment and treatment planning tool designed to assist in assessing the level of suicide risk and factors associated with suicidal thoughts. Six five-point Likert scales rate the degree of psychological pain, stress, agitation, self-hopelessness, self-hate, and overall suicide risk; and additional open-ended questions ask participants to elaborate upon these factors (e.g., “What I find most painful is…”). An earlier version of the form has demonstrated good convergent validity of these rating items with other established measures [55].

In addition, the SSF-4 has items which rate the degree to which participants attribute their suicidal thoughts and feelings to themselves (internal) or others (external), as well as their desire to live and their desire to die. Participants are also asked to make a list of their reasons for living versus their reasons for dying. The form then directs the interaction towards seeking solutions, via the question “the one thing that would make me no longer suicidal would be?” before the clinician gathers information regarding 14 risk factors for suicide (e.g. access to means, history of suicide attempts, substance use). The participant and clinician will document on the SSF-4 the agreed aftercare and stabilisation plans (e.g., “Things I can do to cope differently when I am in a suicide crisis”). The SSF-4 will be repeated at each contact with the clinician.

In the aftercare plan, participants will be asked to set personal goals, consider the values underpinning the goals, short-term and long-term action plans, their strengths and resources, and how to measure successful goal achievement. The aftercare plan, along with the stabilisation plan, will form the basis for individualised ongoing support, and will also be shared with the participant’s nominated general medical practitioner and other relevant stakeholders, with permission. Should family or other support people nominated by the participant attend the session, they will be provided with education on suicide risks and strategies to assist the participant to maintain progress toward his/her goals.

Peer workers will provide follow-up support sessions primarily via telephone (and several face-to-face) three times per week for four weeks; tapering to weekly should the intervention extend to 12 weeks. Each session will be approximately 30 min in duration. Participants will be coached through the steps in their aftercare plan using the framework of the GROW coaching model. Peer workers are trained in the SafeSide model [71] of risk formulation and will escalate to the mental health clinician should they be concerned about a participant’s level of risk.

The clinician and peer worker will meet for discussion and clinical review every two weeks, where they will consider the participant’s level of risk and progress, identify any barriers to progression and strategies to address these, and document any linkages to other services the peer worker has facilitated.

The mental health clinician will meet with the participant again at week four, together with the family/carer, if relevant. This face-to-face session will involve review of the aftercare and stabilisation plans, implementation of adjustments if indicated with a view to discharge from the service if appropriate. The participant and clinician will conduct the SSF-4 together and discuss any changes that may have occurred on the measures. Participants will be considered suitable for discharge when it is felt that their level of risk is appropriate relative to their level of support and the services with which they are engaged. If the participant is deemed suitable for discharge at this time, a discharge plan will be developed in collaboration with their peer worker and their family/carers. The participant and their family/carer (if relevant) will engage in relapse prevention planning and discharge letters will be sent to the participant’s general medical practitioner and any other relevant support services. Prior to discharge, the participant will complete the post-intervention outcome measures. If the participant is not deemed suitable for discharge at their week-four appointment with the clinician, the intervention may extend for up to a further eight weeks. Participants who receive 12 weeks of service and still present with elevated risk will be transitioned to other longer-term options, such as local health district mental health services.

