### Study design

A controlled non-randomised two group (intervention vs treatment-as-usual (TAU) control) design will be used to test the primary hypotheses (hypotheses 1–3), following the intention-to-treat method. The secondary objectives of the study will be evaluated using a pre- and post-intervention repeated measures design (hypothesis 4), in which the intervention group (i.e. participants of the Aftercare intervention) will complete self-report questionnaires prior to their initial intervention session, and again at the time of their discharge appointment from the service.

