### Data handling

Primary outcome data of re-presentations to an emergency department and other local health district data on hospital admissions, community mental health and mental health outcomes will be extracted and de-identified by the Centre for Health Research Illawarra Shoalhaven Population (CHRISP), a research centre which performs data linkage through a partnership between the local health district and the University of Wollongong. Deaths attributable to any cause will be obtained from NSW death registration data held by the NSW Centre for Health Record Linkage (CHeReL). The researchers with be provided with the de-identified coded data.

Secondary outcome data (suicide risk factors) will be collected by the Aftercare service prior to the participant attending their initial session with a mental health clinician and again at the time of their final (discharge) session with the clinician. For Aftercare participants who consent for their data to be included in the study, the data will be de-identified and coded within the Aftercare service, prior to being provided to the researchers.

Data transfers and storage will comply with national and state legislation, national ethics principles and University of Wollongong, local health district and the CHRISP data management policies.

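### Baseline scales are fixed before the first clinician session, but the discharge scales have no matching rule and read as coming after the review and discharge judgement

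*Protocol article*

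**What the plan says.** **Baseline.** Three places in the protocol article agree.
- Study design says that the intervention group "will complete self-report questionnaires prior to their initial intervention session, and again at the time of their discharge appointment from the service".
- The Aftercare intervention section puts the scales after the information sheet and consent: "Following this, they will complete the pre-intervention measures via tablet computer". The clinician session and its SSF-4 are described next.
- Data handling likewise has them collected before the participant attends the initial clinician session.

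**End of treatment.** The same places are looser.
- Study design names only the discharge appointment.
- Data handling says "again at the time of their final (discharge) session with the clinician".
- The Aftercare intervention section describes the week-four visit as a review of the plans, then "The participant and clinician will conduct the SSF-4 together and discuss any changes that may have occurred on the measures", then the discharge criterion: "Participants will be considered suitable for discharge when it is felt that their level of risk is appropriate relative to their level of support". A discharge plan, relapse-prevention planning and discharge letters follow for those judged suitable. Only then comes "Prior to discharge, the participant will complete the post-intervention outcome measures". For those not judged suitable, "the intervention may extend for up to a further eight weeks".

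**Analysis.** The Data analysis section compares pre and post scores within the intervention group by paired t-test or Wilcoxon signed-ranks test, with a Bonferroni correction. No control group completes these scales.

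**The concern.** A pre-post comparison without controls assumes that the two scores differ only because of what happened between them. Here the setting of the measurement may differ too. The baseline score is a self-report made before any contact with the clinician. The post score, as the procedure reads, follows a session in which the participant has rated suicide risk with the treating clinician, talked through change and taken part in discharge planning.

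The content overlaps. The SSF-4 has the participant rate stress and hopelessness, among other things. Stress (DASS-21) and hopelessness (BHS-SF) are also hypothesis 4 outcomes. At baseline the scales come before that joint rating; at the end they appear to follow it.

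If the order moves scores at all, every scale is exposed at the post visit and none at baseline. A larger sample does not remove such a shift, and Bonferroni addresses multiplicity rather than a shift common to the scales. There is no control change to subtract, and the Limitations section mentions only self-selection.

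**Working it through.** The point is about order of events, so the main check is a comparison of the text. The protocol states no power, effect size or sample size for these scales, so there is no figure to reproduce.

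**Step 1: what is fixed.**

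| Section | Baseline | End of treatment |
|---|---|---|
| Study design | before the first session | tied to the discharge appointment; order not stated |
| Aftercare intervention | after consent, before the clinician session | before discharge; sentence placed after SSF-4, judgement and planning |
| Data handling | before the first session | tied to the final session; order not stated |

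Baseline is fixed in all three places. The post measure is fixed in none.

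**Step 2: whether the later order rests only on sentence sequence.** Not entirely.
- Data handling ties the post scales to the final (discharge) session.
- Suitability for discharge is judged at the week-four appointment, and extension follows if the person is not judged suitable.
- A week-four visit therefore becomes the discharge session only once that judgement has been made there.
- So for week-four discharges the scales follow the judgement, unless everyone completes them on arrival. The article does not say that they do.
- For later discharges the date may be known beforehand, and the fortnightly staff reviews could anticipate a week-four discharge. The inference is weaker in those cases.

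**Step 3: illustration of sensitivity.** Inputs:
- Pairs: n = 75 (Sample size and statistical power) if all are complete; n = 40 is an assumption to show incomplete follow-up.
- Scales: seven (depression, anxiety, stress, hopelessness, belongingness, burdensomeness, psychological distress), so two-sided α = .05/7 = .0071.
- Shift δ, in SDs of the difference score, due to measurement conditions alone with no true change: assumed 0 to 0.3. The documents give no value.

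Formula: chance of a false improvement on one scale = P(T > t_crit), where T is non-central t with n − 1 degrees of freedom and non-centrality δ√n, and t_crit is the upper α/2 point of central t.

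- n = 75: t_crit = 2.77, √75 = 8.66
- n = 40: t_crit = 2.84, √40 = 6.32

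| δ | δ√75 | false improvement, 75 pairs | δ√40 | false improvement, 40 pairs |
|---|---|---|---|---|
| 0 | 0 | 0.4% | 0 | 0.4% |
| 0.1 | 0.87 | 3.3% | 0.63 | 1.8% |
| 0.2 | 1.73 | 15.9% | 1.26 | 6.9% |
| 0.3 | 2.60 | 43.8% | 1.90 | 19.0% |

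The 0.4% at no shift is half of .0071, because only the improvement tail is counted.

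**The case against.** The strongest reply is that the article does not actually set the order. Completion before discharge is compatible with completion before the clinician contact. The paragraph is not strictly chronological, because the discharge letters are mentioned ahead of the scales. The measures on which change is discussed are most naturally the SSF-4 ratings; if they included the outcome scales, those would have been completed before the discussion. This stands in part: the order is partly inferred, and the text does not prove that every post score follows the decision. It does not remove the missing rule, or the week-four logic in Step 2.

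A reader might also infer that participants complete the scales having just been told they have improved enough to leave, so that all seven differences are biased towards hypothesis 4. The documents do not support that. The discharge criterion is risk relative to support and services, not symptom improvement. Some participants finish 12 weeks with elevated risk and move to longer-term services. Nothing says that the scores inform the decision. The recall windows of the BHS-SF (past week) and K-10 (past four weeks) would temper a momentary lift.

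It can be said, too, that the point in a visit at which a questionnaire is handed over is operational detail that an article may leave out, and Treatment Fidelity refers to documented service procedures. But this article does give the order at baseline, and it describes a different one at the end. The point is that contrast, not a missing detail.

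Finally, enrolment was expected to cease in November 2019 and the article appeared on 26 October 2019, so a new visit order would reach few participants. That stands, and it moves weight to how visits already held are reported.

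**Conclusion.** The point holds in a limited form. Baseline self-report is fixed before the first clinician session. The post measure has no equivalent rule, and the only procedural description reads as completion after the joint SSF-4, the discussion of change and the discharge judgement, most firmly for week-four discharges. The two scores may therefore be taken under different conditions in a comparison with no control group.

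Bias towards improvement is plausible but not demonstrated. Its size cannot be estimated from the documents, and the 3% to 44% range (75 pairs) or 2% to 19% (40 pairs) rests wholly on the assumed 0.1 to 0.3 SD shift. Only secondary hypothesis 4 is touched; hypotheses 1 to 3 rest on hospital and death records. The importance is minor to moderate: an avoidable asymmetry that is cheap to correct.

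**What to change.** Reconcile Study design, Aftercare intervention and Data handling so that all three state one rule: the scales are self-completed on arrival, before the clinician contact and the SSF-4, at the week-four appointment and at any later discharge appointment, mirroring the baseline procedure. The discharge rule itself stays as it is. Where a week-four visit ends in extension, keep that set as an interim score and use the set from the later discharge appointment as the post score.

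For visits already held, report whether the scales were completed before or after the session where this is known, show change by that order, and state the asymmetry as a limitation of the hypothesis 4 results.

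The cost is one additional questionnaire set for participants who are extended. No new visit or instrument is needed. The retrospective part depends on completion times having been recorded; where they were not, only the limitation statement is available.

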### Data analysis

Analyses will be conducted using the Statistical Package for the Social Sciences version 25 [85] and SAS v9.4 [86]. Primary analyses will be conducted according to the intention-to-treat approach. Presentations to an emergency department with a repeat suicide-related event and for all-cause death will be compared between the two non-randomised groups (intervention vs control) using a Kaplan Meier plot where the initial presentation to an emergency department is designated as time zero, and using censoring. A log-rank test will compare the Kaplan Meier curves of the two groups.

A negative binomial regression model will be applied to the data to estimate the effect of the intervention on re-presentation rates, accounting for varying lengths of follow-up period and adjusting for service and person-level characteristics (e.g. facility, age, sex, indigenous status) and censoring.

To investigate the impact of the service on suicide risk factors (secondary outcome measures), a comparison of pre- and post-intervention outcome measures will be conducted for participants of the intervention using paired t-tests, or a Wilcoxon signed-ranks test (if the sample is non-normally distributed), adjusting for multiple comparisons (Bonferroni correction).

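### Hypothesis 4: the post-intervention scales are collected only at discharge, whose timing depends on a clinician's risk judgement, so the uncontrolled pre-post change can lean toward improvement by an amount the protocol does not let us fix

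*Protocol article*

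**What the plan says.** Three sections of the protocol article place the post-intervention measurement at discharge, and none gives a fixed week.

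- Study design: the questionnaires are completed before the first session and "again at the time of their discharge appointment from the service".
- Aftercare intervention: "Prior to discharge, the participant will complete the post-intervention outcome measures".
- Data handling: the scales are collected "again at the time of their final (discharge) session with the clinician".

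The Aftercare intervention section also says what decides discharge: "Participants will be considered suitable for discharge when it is felt that their level of risk is appropriate relative to their level of support". That sentence goes on to include the services the participant is engaged with. A participant not found suitable at week 4 continues: "the intervention may extend for up to a further eight weeks". At the end of that period, "Participants who receive 12 weeks of service and still present with elevated risk will be transitioned to other longer-term options". The passage does not say whether this last group completes the scales.

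For the analysis, Data analysis states that "a comparison of pre- and post-intervention outcome measures will be conducted for participants of the intervention using paired t-tests", or a Wilcoxon signed-ranks test, with a Bonferroni correction. The stated purpose is to investigate the impact of the service. Intention-to-treat is stated for the primary analyses only.

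**The concern.** When the second measurement is taken depends on how the participant is doing. A person judged ready at week 4 is measured then; a person not judged ready is measured later, at a point again chosen by that judgement or by the end of service.

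The judgement and the outcomes are related by the protocol's own description. The Suicide Status Form (SSF-4) is completed with the clinician at the week-4 session. It rates stress, self-hopelessness and overall suicide risk, and hypothesis 4 includes stress and hopelessness. The article says of the rating items: "An earlier version of the form has demonstrated good convergent validity of these rating items with other established measures". It gives no coefficient.

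Stopping at a favourable reading makes the post score look better than the baseline score even if the underlying state is unchanged. A paired test also uses only people with both scores. The Bonferroni correction controls chance findings across seven scores but does not remove a bias. Limitations discusses self-selection between the groups and does not mention this mechanism. At stake is a result that would be presented as the effect of the service on suicide risk factors.

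**Working it through.** The protocol states no effect size, SD or power for hypothesis 4, so there is no figure of its own to reproduce.

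**From the protocol.** Intervention group n = 75; seven scores; paired test, taken here at .05/7 = .00714. The nominal false rate in the improvement direction is half of that, 0.36% per score. Discharge falls between week 4 and week 12.

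**Assumed, because the documents give no values.**
- Correlation r between discharge judgement and score: 0 to .7.
- Score stability between visits with no true change (ICC): .5 to .7.
- Chance p of being judged suitable at one decision: .5 to .7.
- Discharge decisions: two (weeks 4 and 12) or three (weeks 4, 8 and 12).

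**Model with no true change.** Score = person mean + visit noise, variance 1, lower is better. A participant is discharged when the judgement falls below a threshold z with Φ(z) = p.

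*Step 1, those discharged at week 4.* Their expected week-4 score is −r·φ(z)/p and their expected baseline is −r·ICC·φ(z)/p. The spurious change is therefore −r(1 − ICC)·φ(z)/p.

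*Step 2, two decisions, everyone measured by week 12.* The remainder are measured at week 12 whatever their state, so their expected change is 0. Overall bias = −r(1 − ICC)·φ(z).
- Smallest non-zero case, r = .3, ICC = .7, p = .7 (φ = .348): .3 × .3 × .348 = 0.03 SD.
- Largest case, r = .7, ICC = .5, p = .5 (φ = .399): .7 × .5 × .399 = 0.14 SD.

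*Step 3, three decisions.* Simulation, n = 75, 4,000 replicates per scenario:

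| Scenario | Spurious improvement (SD) | False improvement per score |
|---|---|---|
| r = 0 | 0.00 | 0.2–0.4% |
| r = .3–.7, everyone measured by week 12 | 0.04–0.21 | 1.3–18.6% |
| r = .3–.7, never-suitable unmeasured (3–21% missing) | 0.05–0.31 | 1.5–38.5% |
| Everyone measured at fixed week 4 | 0.00 | 0.2–0.5% |

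*Step 4, is the week-4-discharge subgroup a clean check?* No. By step 1 its bias at r = .7, ICC = .5, p = .5 is .7 × .5 × .399/.5 = 0.28 SD. That exceeds the full-sample 0.14 (two decisions) or 0.21 (three), because the same judgement selects the subgroup.

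**The case against.** The case against has real force on size.

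- **The criterion is not low risk.** It is risk relative to support and services, with no cut-off on any outcome scale. A participant with unchanged scores could be discharged once supports are in place. The correlation could be low, and at r = 0 the bias vanishes. This stands.
- **High correlations are hard to justify.** If the judgement is independent of a scale's measurement error, its correlation with the score cannot exceed the square root of the reliability. For the DASS-21, the alphas in the protocol give √.73 = .85 for anxiety and √.81 = .90 for depression and stress. Values near .9 need an almost perfect judgement.
- **Few discharge decisions are documented.** Only week 4 has a stated decision with the participant. The two-weekly review is between clinician and peer worker and is not described as a discharge decision.

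A reader might infer a bias of 0.14 to 0.36 SD. That range needs correlations of .6 to .9 and decisions every two weeks from week 4, neither of which is in the documents. The K-10 also asks about the past four weeks, so scores two weeks apart would not vary independently.

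A reader might also infer that only those who have recovered are measured. The documents do not support that: service ends at week 12 regardless, and the final-session wording in Data handling can be read to include people leaving then. Handling of missing post scores may sit in an analysis plan not shown.

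Finally, hypothesis 4 concerns change following the intervention, and week 4 is mid-intervention for extended participants. That is a reason to add a fixed-time score, not to replace the discharge score.

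What the objection does not remove is the timing. It is fixed in this document, and no later analysis can recover week-4 scores that were never collected.

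**Conclusion.** The point holds in a limited form. As written, the time of the post score depends on a judgement that overlaps the outcomes, and any positive link between the two pushes the uncontrolled paired comparison toward improvement. The direction follows from the design; the size cannot be taken from the documents. Under the stated assumptions it is 0 to about 0.2 SD if everyone is measured by week 12, and up to about 0.3 SD if those never judged suitable go unmeasured. Losses before any discharge session are not quantified.

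Only secondary hypothesis 4 is affected. It would be wrong to infer that the main comparison is compromised by this: hypotheses 1 to 3 use linked hospital and death records over 12 months. Recovery after a crisis with no comparison group is a separate limit, which a fixed-time measure would not cure.

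**What to change.** 1. Administer the same scales to every consenting participant at the week-4 clinician appointment already scheduled, whether or not they are discharged. Keep the discharge score as well.
2. Report baseline-to-week-4 change in all enrolled participants, for example with a mixed model, alongside the discharge comparison. Note that week 4 is mid-intervention for those whose service is extended.
3. Reconcile the Aftercare intervention and Data handling sections on whether participants transitioned at week 12 complete the measures.
4. For participants already enrolled without a week-4 score, report when post scores were taken and how many were completed. Do not use the week-4-discharge subgroup as an unbiased check.
5. Describe the result as within-person change, not as the impact of the service, and add the timing issue to Limitations.

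The cost is one extra questionnaire for extended participants and a minor amendment. Enrolment was expected to end in November 2019 and the article appeared in late October 2019, so most participants may already lack the week-4 score; items 3 to 5 then carry most of the benefit. No change to discharge practice is implied.
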